### Sample size

SSI rates following breast reconstruction vary in the literature, from 1% a 30%
[1,4,5,9-11]. We considered clinically relevant a 10% difference in SSI rate
[35]. Specifying an acceptable Type 1 error of 5%, and Type 2 error of 20%, the estimated sample size was 100 patients per arm.

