### Patients’ assessments of dressing wear time

On their return in the second week after operation, patients will be asked to rate their dressing wear time with regard to safety, comfort and convenience, by the use of a 5-point rating scale (Table 
2)
[35].

**Table 2 T2:** Patients’ self-assessment of dressing wear time

Please rate the **dressing wear time** following your breast surgery in regard to:				

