### Statistical analysis

The rejection level for the null hypothesis will be fixed at 5% (α ≤ 0.05). The Mann-Whitney test will be used to compare groups I and II with regard to age, BMI and duration of operation.

The Fisher test will be used to compare groups I and II regarding SSI occurrence. Logistic regressions will be applied to detect significant associations between variables such as age, BMI and duration of operation and the incidence of SSI.

For inter-group assessment of skin colonization, the Mann-Whitney test will be used to compare groups I and II pre-dressing and at the sixth postoperative day. These tests will be applied independently for each medium used. Because skin colonization could play a role in SSI rates, an intra-group assessment of skin colonization will also be performed. For this assessment, in group I Friedman two-way analysis of variance will be used to assess the differences in number of CFU among the three moments (pre-dressing, first and sixth postoperative day). Whenever the difference is significant, the Friedman two-way analysis of variance will be complemented by the multiple comparisons test to determine which moment significantly differed from the others. In group II, the Wilcoxon test will be used to compare the number of CFU pre-dressing and at the sixth postoperative day.

The Kolgomorov-Smirnov test will be applied to compare the two groups regarding patients’ assessments of safety, comfort and convenience. The Fisher test will be used to compare groups I and II regarding patients’ choice (one day or six days).

Statistical analysis will be performed using SPSS (Statistical Package for Social Sciences, Inc., Chicago, IL, USA) v.18 and Bioestat 5.0 (Instituto de Desenvolvimento Sustentável Mamirauá, Belém, PA, Brazil).

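### The Kolmogorov-Smirnov test on five-category ratings runs at under 1% instead of 5% and loses about half its power for moderate shifts

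*Protocol article*

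**What the plan says.** The protocol article, under Patients' assessments of dressing wear time, has patients rate three items at the second-week visit "by the use of a 5-point rating scale". Table 2 gives the categories: Excellent, Very good, Good, Fair and Poor.

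The Statistical analysis section names the test: "The Kolgomorov-Smirnov test will be applied to compare the two groups regarding" these three ratings. It mentions no exact or permutation p-value and no handling of ties, and it sets the significance level at 5%.

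The same section uses the Mann-Whitney test to compare the groups on age, BMI, duration of operation and colony counts.

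Under Sample size, "the estimated sample size was 100 patients per arm"; that number was set for the infection rate. No effect size or power is given for the ratings. Study aims lists patients' perceptions of the three items among the secondary aims.

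**The concern.** The reference distribution of the two-sample Kolmogorov-Smirnov statistic is derived for continuous data, in which the maximum gap D is searched over many distinct points. A five-category scale has only four cut-points. A maximum over four points is usually much smaller under the null hypothesis than a maximum over a continuum, so the standard p-value is too large.

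The test is also an omnibus test of any difference between distributions. The Discussion treats perceptions directionally: leaving the wound uncovered may be more convenient, a dressing may be more comforting, and patients may prefer longer wear. Those are questions of whether one arm rates higher than the other, which a rank test addresses directly.

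At stake is a declared secondary aim. A moderate real difference in how patients rate one-day and six-day wear would more often than not be reported as non-significant because of the test chosen. If infection rates turn out similar, these ratings would be a natural basis for the recommendation the trial hopes to support.

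**Working it through.** **Inputs from the protocol.** 100 patients per arm; 5% level; five ordered categories; Kolmogorov-Smirnov test with no p-value method stated. The plan states no power for the ratings, so there is no figure to reproduce.

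**Assumptions.** Two-sided testing; full data on 100 per arm; the standard asymptotic p-value; rating distributions and effects as given below.

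**Step 1: the rejection threshold.** Z = D × √(n1·n2/(n1+n2)) = D × √(100·100/200) = 7.071 × D, and p ≈ 2·exp(−2Z²), the leading term of the Kolmogorov series (later terms are negligible here).

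- D = 0.19: Z = 1.344, p = 0.054, not significant.
- D = 0.20: Z = 1.414, p = 0.037, significant.

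With 100 per arm D moves in steps of 0.01, so the test rejects only when D is at least 0.20.

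**Step 2: a bound that needs no assumed rating distribution.** Under the null hypothesis, the exact binomial probability that two arms of 100 differ by 20 or more patients at a single cut-point is at most 0.57%, reached when the cumulative proportion is 50%. There are four cut-points, so the true type I error cannot exceed 4 × 0.57% = 2.3%. More than half of the 5% is lost whatever the ratings look like.

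**Step 3: simulated type I error.** Two multinomial samples of 100, 40,000 runs for each of six assumed distributions: uniform, symmetric (10/20/40/20/10%), skewed towards good (40/30/20/7/3%), ceiling (60/25/10/4/1%), a stronger ceiling, and a milder skew.

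- Kolmogorov-Smirnov: 0.1% to 0.9%.
- Tie-corrected Mann-Whitney: 4.9% to 5.2%.
- Kolmogorov-Smirnov on untied continuous data at the same sample size: about 3.5%. Most of the conservatism therefore comes from the ties.

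**Step 4: why power suffers, by example.** Take 40/30/20/7/3% in one arm, with cumulative proportions 40, 70, 90 and 97%. Halving each cumulative odds (a common odds ratio of 2 towards worse ratings) gives 25.0, 53.8, 81.8 and 94.2% in the other arm. For instance, 0.40/0.60 = 0.667, halved is 0.333, which is 25.0%. The gaps are 15.0, 16.2, 8.2 and 2.8 points. The largest true gap, 16.2 points, lies below the 20 points the test needs. Simulated power is 42% for Kolmogorov-Smirnov and 77% for Mann-Whitney. With the same odds ratio towards better ratings it is 40% and 74%.

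**Step 5: power over the six distributions** (proportional-odds shift, 40,000 runs each).

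| Odds ratio | Kolmogorov-Smirnov | Mann-Whitney | Share of power kept |
|---|---|---|---|
| 1.49 | 4–13% | 25–35% | 0.15–0.36 |
| 1.65 | 8–22% | 38–51% | 0.21–0.43 |
| 1.82 | 15–34% | 51–67% | 0.30–0.51 |
| 2.01 | 26–48% | 65–79% | 0.40–0.60 |
| 2.23 | 39–62% | 77–89% | 0.50–0.70 |
| 2.72 | 68–85% | 93–98% | 0.73–0.87 |
| 3.32 | 89–96% | 99–100% | 0.90–0.97 |

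**Step 6: sensitivity to the p-value method.** A permutation p-value that conditions on the ties (three of the distributions, 1,500 runs with 1,000 permutations each) has type I error 2.5% to 3.5% and power of about 65% at an odds ratio of 2.01. For the same distributions the asymptotic version gives 35% to 42% and Mann-Whitney 74% to 78%.

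**The case against.** The strongest reply is that the result depends on a p-value method the article does not state, and that a condensed article may leave this to a fuller document. With a permutation p-value the loss against Mann-Whitney is about one-seventh, not half. This stands as a condition on the size of the loss. It does not remove the problem: the test is named without any such qualification, and the permutation version still trails Mann-Whitney for shifts.

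Second, the Kolmogorov-Smirnov test can be the better one. For a pure difference in spread it had 88% power against 6%, and for changes at a single threshold about 53% against 25% to 49%. This is true, so the loss is not universal. But the Discussion gives reasons for ratings to be higher or lower in one arm and none for a difference in spread alone.

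Third, an odds ratio of 2 is the reviewer's choice, and large differences would be detected either way. The table bears this out.

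Fourth, the direct question of whether patients would choose one or six days is tested by Fisher's test and is unaffected, and a conservative test creates no false positives. Both points are correct and limit the seriousness. The three ratings nevertheless belong to a secondary aim in their own right.

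Finally, the variables for which the plan uses Mann-Whitney are not ordinal ratings, so the plan does not contradict itself. The choice is poor, not inconsistent.

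**Conclusion.** The concern holds. With the standard p-value, the named test cannot reach even half of its stated 5% level on a five-point scale at 100 per arm, and its type I error was below 1% in all six distributions examined. For moderate shifts (odds ratios of about 1.8 to 2.2) it keeps roughly 30% to 70% of the power of Mann-Whitney, which is about half in the middle of that range.

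The bound of 2.3% needs no assumption about how patients rate. The power figures rest on assumed rating distributions, proportional-odds shifts, complete data and the asymptotic p-value. The problem is confined to three secondary comparisons. It should be corrected, but it does not threaten the primary result.

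**What to change.** Replace the sentence on the Kolmogorov-Smirnov test so that each of the three items is compared between groups by the tie-corrected Mann-Whitney (Wilcoxon rank-sum) test. Report with it either a common odds ratio from a proportional-odds model or the Mann-Whitney probability (the chance that a patient in one group rates higher than a patient in the other, ties counting one half), with a 95% confidence interval.

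If sensitivity to any difference in distribution is really wanted, the alternative is to keep the Kolmogorov-Smirnov test and state that its p-value comes from a permutation distribution that respects the ties. This brings the type I error closer to 5% but gives less power for shifts.

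The cost is one sentence. Mann-Whitney is already planned in the same section, and no data collection or sample size changes. What is given up is sensitivity to differences in spread or at a single threshold. Trial status reports recruitment still under way, with 134 of the planned 200 patients operated on, so the change can be made and dated before the ratings are analysed.

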## Discussion

SSI is a major source of adverse events in patients undergoing breast cancer surgical procedures, generating psychological issues, increased duration of hospitalization and costs, as well as delay in commencing postoperative adjuvant therapies
[2,5,11]. Consequently, surgeons should make a determined effort to prevent SSI. As protocols and guidelines should be founded on evidence-based medicine principles, well-designed studies are essential to support or to adjust clinical practice
[20].

Wound management is a key area in preventing SSI
[21]. However, few studies have focused on the management of the wound after closure as a method of reducing infection
[34]. This randomized trial focuses on the influence of dressing wear time in SSI rates. Since the greater the degree of surgical wound contamination, the higher the risk for infection
[2,19], skin colonization assessment is a secondary aim of this study.

The management of surgical wounds should involve the principle of minimizing harm, and patient preference and tolerance must also be considered
[30]. Thus, assessment of patients’ perceptions of dressing wear time is another secondary aim in this trial. Some authors pointed out that omitting a dressing after the first 24 postoperative hours could be convenient for patients, allowing them to carry out their personal hygiene more easily
[24]. However, other authors observed that dressings are comforting to patients by masking their scars without increasing SSI rates
[23,26,35]. Considering the mutilating characteristics of breast cancer treatment, we hypothesize that patients, particularly those who undergo immediate breast reconstruction, might prefer to keep their dressings in place for a longer time, thus delaying the moment of seeing their reconstructed breasts.

CDC’s guidelines for managing surgical wounds that are closed primarily instruct patients to keep their wounds dry and covered for 24 to 48 hours
[19], but the ideal dressing wear time following breast surgery remains an unsolved issue. The results of this trial may support standard recommendations regarding dressing wear time after breast reconstruction.

## Trial status

Recruitment is on-going (134 patients had been operated on by the end of December 2012).

## Abbreviations

CDC: Centers for Disease Control and Prevention;SSI: surgical site infection;BMI: body mass index;CFU: colony forming units;HM: hypertonic manitol;EMB: eosin-methylene blue
